### Recruitment {15}

The recruitment process will take place the day before the surgery in the cardiac general ward, Peking Union Medical College Hospital, Beijing, China. Following manually screening the electronic health records, patient enrollment will be initiated according to the inclusion and exclusion criteria listed above.

## Assignment of interventions: allocation

### Sequence generation {16a}

The randomization of six TEE operators who are willing to participate in our trial will be accomplished via SASS software. They were evenly distributed in a 1: 1 ratio into the PReTEE group and conventional TEE group.

### Concealment mechanism {16b}

The concealment will be targeted for all TEE operators and investigators. The statistical analysts will also not be informed of the allocation groups until the final analysis is achieved.

### Implementation {16c}

The computerized randomization of TEE operators will be completed once the trial is started. Patient enrollment will be accomplished by the investigators.

## Assignment of interventions: blinding

### Who will be blinded {17a}

Enrolled patients, experts, data recorders, and outcome/data analysts are not aware of the TEE allocation groups. Further, the attending anesthesiologists and cardiac surgeons will also be blinded in the entire process of study conduction.

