### Intervention description {11a}

General cardiac anesthesia induction and maintenance will be prescribed at the chief anesthesiologist’s discretion. CPB procedure at our institute complies with a standardized pattern. The separation of CPB is ended with the administration of protamine and the removal of the venous and arterial cannulas. All patients during intraoperative periods will receive a round of TEE examination before and after CPB routinely. Hemodynamic parameters and TEE findings are two major determinants in the process of CPB separation. Following the completion of surgical procedures, patients will be admitted to the intensive care unit for further advanced monitoring and therapy. The timing of transfer from intensive care unit to the general ward will depend on patient physical recovery status.

When the process of CPB separation initiated, the TEE probe is immediately inserted by the TEE operators. Then they are required to remove and rotate the probe and to promptly detect the leading causes of complex CPB separation. After the probe is well inserted, the time taken in seconds till TEE scan completion will be measured by the study recorder. The etiology interpretations and their corresponding TEE views will also be reported to the recorder by operators and simultaneously kept in a form of questionnaire (Supplemental file 1). The maximum time for TEE sequence scanning permitted is 120 s. The number of both junior TEE operators and eligible patients available at our institute are to some extent of limitation; therefore, TEE examination for each patient is not conducted by equal numbers of operators stratified by allocation groups. During patient examinations by operators and the expert, the TEE probe is kept still.

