The successful diagnosis is defined as the correct cause of discrimination within the specified 120 s. If an operator does not report any diagnoses or reports the uncorrected ones, a failure will be assigned. All TEE examinations in both groups will be supervised by the expert, who guarantees the safety of this study but does not facilitate the image obtainment or interpretation. The TEE results within this trial will also be finalized by the expert. TEE operators who finish the sequence scan and diagnosis report will immediately leave the operating room, therefore precluded from observing the expert’s TEE examination. The TEE expert finally will rate the cause discrimination per examination by the operators with a 5-point scale system (1 point, absolutely wrong; 2 points, wrong; 3 points, average; 4 points, correct; and 5 points, absolutely correct) (Supplemental file 1). There is no application of scoring system on the clarity of TEE view acquisition, as the TEE operators participating in this trial have obtained TEE manual skills. During the study period, the TEE machine we employ is Philips Ultrasound iE33 and the probe is Philips Ultrasound X7-2t.

Following the completion of TEE operators’ assessment, the TEE expert will routinely perform a standard comprehensive TEE examination. The cause provided by the TEE expert will be directly communicated to the attending anesthesiologist and cardiac surgeons, independent from this study, referred as therapeutic approach.

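### The expert and the data recorder are declared blinded, yet their described roles make the arm readily identifiable, so the judgement that decides the primary outcome is not masked as stated

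*Protocol article*

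**What the plan says.** The blinding section (Who will be blinded {17a}) declares: "Enrolled patients, experts, data recorders, and outcome/data analysts are not aware of the TEE allocation groups".

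Intervention description {11a} gives two of these people the following tasks:

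- **Expert, during the scan:** "All TEE examinations in both groups will be supervised by the expert, who guarantees the safety of this study". The expert does not help with image acquisition or interpretation.
- **Expert, after the scan:** "Following the completion of TEE operators’ assessment, the TEE expert will routinely perform a standard comprehensive TEE examination". The expert also settles the trial's findings ("The TEE results within this trial will also be finalized by the expert") and scores the operators: "The TEE expert finally will rate the cause discrimination per examination by the operators with a 5-point scale system".
- **Recorder:** times each scan in seconds and receives the diagnosis together with the views. "The etiology interpretations and their corresponding TEE views will also be reported to the recorder by operators". The section Data collection and management repeats this.

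Explanation for the choice of comparators {6b} defines the arms. Three operators follow a fixed three-view sequence and three scan without restriction, and this is allocated before the trial starts. The primary endpoint in Outcomes {12} counts a diagnosis as correct when it agrees at least 70% with the expert's TEE. Statistical methods {20a} censors failed diagnoses in the Cox model.

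**The concern.** The only thing that separates the arms is what happens on the screen during the scan. A supervisor watches it, and a recorder is told which views were used. Calling both unaware of the arm claims a protection that the described conduct does not provide, and a reader of the results would credit the trial with it.

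This matters more than usual because the same expert supplies the reference standard and judges the operator against it. The protocol guards one direction: operators leave the room before the expert scans. It describes nothing for the other direction, since the expert has supervised the operator's scan before making the reference diagnosis. Knowledge of the arm could therefore affect both the reference and the judgement of whether the operator matched it. The recorder's exposure matters less but is not irrelevant, because the recorder's timing feeds the time-to-event analysis.

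**Working it through.** The blinding statement carries no figure. The protocol's one related calculation, 42 examinations for 90% power at 5% with a hazard ratio of 2.78, is approximately reproduced by the two-sided Schoenfeld formula: 4 × (1.960 + 1.282)² / (ln 2.78)² = 40.2, rounded up to 41. Nothing in this point changes it.

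**Step 1. Declared status against described role**

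| Person | Declared in {17a} | Role in {11a} | Does the role expose the arm? |
|---|---|---|---|
| Expert | Unaware | Supervises every scan in both arms, makes the reference examination, rates the diagnosis | Yes, the view sequence is in front of the supervisor |
| Recorder | Unaware | Times the scan, takes down causes and views | Yes, the views are the feature that defines the arm |

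**Step 2. Persistence.** Arm is fixed per operator. With 46 scans and six operators the average is 46/6 = 7.7 scans each. Once an operator's arm is recognised, it is recognised for all that operator's remaining scans.

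**Step 3. Path to the primary analysis.** Expert's finding → agreement of at least 70% or not → success or failure → event or censored observation in the Cox model. Every link after the first depends on the expert's reference and on the judgement of the match. No separate masked adjudication is described.

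**Step 4. Weight of one scan.** The protocol gives 46 scans in total and randomises operators, not scans, 1:1, so the number per arm is an assumption.

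- Even split of 46: 1/23 = 4.3 percentage points.
- Even split of 42 (the number before the dropout allowance): 1/21 = 4.8 points.
- Uneven split, for example 20 and 26: 1/20 = 5.0 and 1/26 = 3.8 points.

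**Step 5. Illustration for the Cox model.** All inputs here except the total of 46 are assumptions: 23 scans per arm, equal true success p by 120 s in both arms, exponential times, independent scans, and an assessor who upgrades a share b of true failures in the PReTEE arm only.

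- Apparent success in that arm: p₁ = p + (1 − p)b
- Apparent hazard ratio: HR = ln(1 − p₁) / ln(1 − p)
- Expected events: d = 23(p + p₁)
- Chance of a significant result favouring PReTEE: Φ(½√d × ln HR − 1.960), nominally 2.5%

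Worked case, p = 0.6 and b = 0.2: p₁ = 0.68, HR = ln 0.32 / ln 0.40 = 1.24, d = 29.4, probability 8.6%.

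| b | p = 50% | p = 60% | p = 70% | p = 80% |
|---|---|---|---|---|
| 10% | HR 1.15, 5.3% | 1.11, 4.8% | 1.09, 4.3% | 1.07, 3.9% |
| 20% | HR 1.32, 10.4% | 1.24, 8.6% | 1.19, 7.1% | 1.14, 5.9% |
| 30% | HR 1.51, 18.6% | 1.39, 14.6% | 1.30, 11.5% | 1.22, 9.0% |

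At b = 20% the expected number of upgraded scans is 23 × (1 − p) × 0.2, which runs from 2.3 (p = 50%) to 0.9 (p = 80%). One or two generous judgements in one arm are enough for the shifts in that row.

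**The case against.** Supervision by an expert is there for patient safety, so some exposure during the scan cannot be avoided. That stands. It explains the exposure but does not make the blinding statement correct. Where operators from both arms scan the same patient, one reference may serve both, which limits how far the reference itself can favour an arm. The match is still judged for each operator, and the protocol says that operators per patient are not balanced by group.

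Several stronger readings are tempting, and the document does not support them:

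- **That the arm is known.** The text does not say so. A conventional operator may use any views, including the same three. Readily identifiable is as far as the described roles go.
- **That the 5-point rating sets the primary outcome.** The protocol never links that scale to the 70% rule, and the questionnaire is in a supplementary file that is not shown. The narrower statement holds either way: the expert is both reference and rater.
- **That the expert hears the operator's report first.** The report goes to the recorder. Whether the expert hears it is not stated.
- **That operators are falsely described as blinded.** Concealment mechanism {16b} says "The concealment will be targeted for all TEE operators and investigators", but that section concerns allocation concealment, which is compatible with operators later knowing their arm. The blinding section does not list operators.
- **That the rater is partisan.** Nothing says that the expert devised the three-view sequence, and the expert is not among the research team listed under oversight {5d}.
- **That a few misjudged scans equal a given share of the planned effect.** The planning times of 36 s and 100 s are not identified as means or medians. With exponential times, success by 120 s would be about 90% v 56% if they are medians and about 96% v 70% if they are means. No such comparison is drawn here.

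**Conclusion.** The contradiction holds, and it is confined to the expert and the data recorder. The blinding declared for patients and for outcome or data analysts is not disputed here. For the expert it reaches the primary endpoint, because the same person supervises the scan, supplies the reference and rates the diagnosis.

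The firm part of the size is the weight of one scan, about 4.3 points in an arm's success proportion under an even split and 3.8 to 5.0 points under the variants shown. The table of false-positive probabilities only shows sensitivity under invented misrating shares. It is not an estimate of bias in this trial, and the direction of any bias is unknown. The point should be corrected because it touches the credibility of the primary result and the correction is cheap.

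**What to change.** 1. **Correct the blinding section.** State that the expert and the recorder are not blinded during the scan. The allocation concealment section needs no change on this account.
2. **Lock the reference.** The expert writes down and locks the reference diagnosis from the expert's own comprehensive scan before seeing or hearing any operator's report. Communication of the expert's finding to the clinical team stays as it is.
3. **Fix the matching rule.** Specify in advance how agreement of at least 70% is calculated from the reported and reference causes, and whether the 5-point rating has any part in it.
4. **Score masked.** Apply the rule to copies of the report forms with operator identity, views and time removed and the order shuffled. The scorer should preferably be an existing team member who was absent from the scan. If the expert scores, recall is possible with only 46 scans.

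**Cost:** a wording change, some form handling and a short matching rule. No new assessor needs to be hired if an existing team member scores. Scoring happens later than the day of surgery. The bias is reduced and not removed, because the expert still supervises the scans for safety before making the reference diagnosis, and the report should say so as a limitation.

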### Procedure for unblinding if needed {17b}

Unblinding is of necessity if applicable. The unblinded procedures will arise when threatening adverse events or esophageal injuries occur or this trial is completed.

### Data collection and management

 TEE operators are required to remove and rotate the probe and to promptly detect the leading causes of complex CPB separation. After the probe is well inserted, the time taken in seconds till TEE scan completion will be measured by the study recorder. The etiology interpretations and their corresponding TEE views will also be reported to the recorder and simultaneously kept in a form of questionnaire (Supplemental file 1). The maximum time for TEE sequence scanning permitted is 120 s. 

### Plans for assessment and collection of outcomes {18a}

Throughout the trial implementation, the primary and secondary outcomes of interest will be recorded in the form of questionnaires held by the trained recorder.

### Plans to promote participant retention and complete follow-up {18b}

No follow-up visits after patient hospital discharge are designed.

### Data management {19}

Signed informed consent and case report form (CRF) will be stored in a locked cabinet in our department. Patient baseline characteristics and surgical and postoperative information are all manually extracted from electronic database by trained recorders. Data mentioned above and TEE recordings are required to be entered twice into Excel. The rights of data access and process are only provided to authorized researchers, ethnic committees, and medical regulators. Any change to raw data must be noted with actual date and implementors. All statistical analyses should be completely retained in R software.

### Confidentiality {27}

The participants will be allocated an individual trial identification number. Aimed to protect the privacy of participants and patients, their information will be stored within a secure database. All data collected in the process of trial implementation should be stored by the investigators for 5 years. The rights of data access and process will only be accessible to study personnels, ethics committees, and medical regulators.

### Plans for collection, laboratory evaluation, and storage of biological specimens for genetic or molecular analysis in this trial/future use {33}

Not applicable. No biological specimens will be collected.

## Statistical methods

### Statistical methods for primary and secondary outcomes {20a}

The R software will be ultimately employed to perform all statistical analysis. The continuous data will be summarized as median (standard deviation) or median (interquartile range), whereas categorical data as number (percentage). Based on the time to event in the process of estimating the difference regarding diagnostic efficiency between the conventional TEE group and the PRe TEE group, a Cox proportional hazards model will be considered. In the Cox model, we will treat the TEE operators who failed the diagnosis as censored. A *P* < 0.05 will be considered statistically significant.

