### *Trial design* {8}

This is a single-center and randomized controlled trial which will be prospectively conducted at Peking Union Medical College Hospital, Beijing, China. The six TEE operators participating in this trial will be randomly assigned in a 1:1 fashion into the PReTEE group and the conventional TEE group. This protocol strictly conforms to the Standard Protocol Items Recommendation for Interventional Trials (SPIRIT) Checklist (Table 1).

**Table 1 Tab1:** SPIRIT flow diagram. *PReTEE* perioperative rescue transesophageal echocardiography, *TEE* transesophageal echocardiography

	**Enrolment**	**Allocation**	**Post-allocation**	
Timepoint**	**Pre-allocation** **-t**_**1**_	**Preoperative** **0**	**Procedure** **t**_**1**_	***t***_***2***_
Enrolment:				
Eligibility screen	X			
Informed consent	X			
Allocation		X		
Interventions:				
PReTEE			X	X
Conventional TEE			X	X
Assessments:				
Outcome measurements			X	X
Adverse event evaluation			X	X

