## Interventions

### Explanation for the choice of comparators {6b}

Six TEE operators, willing to participate in this trial, are all junior cardiac anesthesiologist fellows at our institute whose accumulation of TEE performances are relatively comparable. They will be randomly assigned into the TEE groups stratified by allocation prior to trial initiation, with three in each group. The three operators in the PReTEE group will be required to accomplish the TEE examinations using a simple sequence of ME 4C, ME AV LAX, and TG SAX. On the other hand, another three in the conventional cohort will perform TEE examinations in a liberal fashion, that is, without any restriction on scan sequence.

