### Sample size {14}

In our preliminary experiment, the time of finding out the cardiac etiologies in the PReTEE group was 36 s, whereas in the conventional group was 100 s. The preliminary results have never been published. Twenty PReTEE exams were performed using the available simulator employed at our center. Considering the apparent reduction of timing of diagnosis, no further PReTEE exams are planned to be conducted in cardiac surgical patients. However, one TEE scanning procedure in the conventional group was implemented for one cardiac patient in the operating room. To achieve a 90% power at a significance level of 5%, 42 TEE examinations should be conducted among eligible patients using a hazard ratio of 2.78. Considering a 20% dropout rate, a total of 46 TEEs are schemed to be consecutively performed. The sample size calculation was achieved using the gsDesign package via R software.

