The major limitation of this study is the small number of TEE operators who will participate in this trial. The TEE operators are all junior cardiac anesthesiologists during the process of trial implementation, without any senior ones involved; it is not sure whether the clinical effects of PReTEE would fluctuate along with the experience of TEE operators. In addition, this is not a multi-center study and extrapolation of results will be limited.

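### Six operators are randomised, but the sample size and the Cox model count scans as independent: the stated 90% power is not delivered, and the 5% error rate is exposed if operators differ

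*Protocol article*

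**What the plan says.** Three sections make the operator the randomised unit. Trial design {8}: "The six TEE operators participating in this trial will be randomly assigned in a 1:1 fashion". Explanation for the choice of comparators {6b} places them "with three in each group". Sequence generation {16a} again describes "The randomization of six TEE operators who are willing to participate in our trial". Neither patients nor scans are randomised. The abstract has these six people perform all 46 scans.

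Sample size {14} counts examinations. It reports that "the time of finding out the cardiac etiologies in the PReTEE group was 36 s, whereas in the conventional group was 100 s", and concludes that "42 TEE examinations should be conducted among eligible patients using a hazard ratio of 2.78", for 90% power at the 5% level. The total is then raised to 46. No number of operators, intraclass correlation or design effect enters.

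Statistical methods {20a} says that "a Cox proportional hazards model will be considered", with failed diagnoses censored and significance at P < 0.05. It names no operator effect, patient effect or clustered variance.

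The Discussion concedes that "The major limitation of this study is the small number of TEE operators who will participate in this trial", but explains this in terms of operator experience and not of error rate or power.

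**The concern.** Each operator contributes about 46/6 = 7.7 scans, all in one arm, so operator is nested in arm. The outcome is the operator's own speed and correctness, and scans by one person share that person's ability. If a quick operator is allocated to one arm by chance, a scan-level model reads this as an effect of the method and attaches too small a standard error to it.

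Two things are at stake. One is whether P < 0.05 from the planned model means what it says. The other is whether a trial with three operators per arm has anything like the stated power.

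**Working it through.** **1. Reproduce the plan's figure.** Inputs from Sample size {14}: HR 2.78 (100/36 = 2.78), 5% level (taken as two-sided), 90% power, 1:1. Schoenfeld's formula for independent observations:

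events = 4 × (1.960 + 1.282)² / (ln 2.78)² = 40.2

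This rounds up to 41, or to 42 if made even for two equal arms. Power at 42 events is 91.2%. The stated 42 is therefore the independent-observations answer, with no allowance for operators.

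**2. Separate the loss from the 120 s cap.** The formula gives events, but the plan uses the result as a number of examinations. With exponential times, 23 scans per arm and every scan usable, expected events are:
- 36 s and 100 s read as means: 23 × [(1 − e^(−120/36)) + (1 − e^(−120/100))] = 23 × (0.964 + 0.699) = 38.2
- read as medians: 23 × [(1 − 2^(−120/36)) + (1 − 2^(−120/100))] = 23 × (0.901 + 0.565) = 33.7

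The protocol does not say which applies. The simulated power of the unadjusted Cox test with no operator variation is about 88% and 84% respectively. This shortfall is due to censoring, not clustering.

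**3. Add operator variation.** The protocol gives no operator SD, so a range is assumed. At SD 0.2 an operator one SD above average has a hazard e^0.2 = 1.22 times the average; at SD 0.5 it is e^0.5 = 1.65 times. The simulation uses 46 scans split 8/8/7 in each arm, normal operator effects on the log hazard and censoring at 120 s. The null case sets 60 s in both arms; the alternative is 36 s v 100 s. The operator-level test is a t test on six log rates, with 4 df and critical value 2.776 instead of 1.960. Ranges span repeated runs and, for power, both readings of 36 s and 100 s.

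| Operator SD | Unadjusted type I error, one scan per patient | Unadjusted type I error, each patient scanned once in each arm, patient SD 0.5 | Power of operator-level t test, one scan per patient |
|---|---|---|---|
| 0 | 5.1-5.8% | 3.6-3.8% | 60-67% |
| 0.2 | 7.1-8.6% | 5.4-5.6% | 52-56% |
| 0.3 | 9.6-10.9% | 7.2-7.9% | 44-48% |
| 0.5 | 16.9-18.2% | 13.6% | 30-32% |

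The operator-level test holds about 5% type I error throughout.

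**4. Limit set by six operators.** With six operators the effective number of events cannot exceed 6/ICC. Setting 6/ICC = 40.2 gives ICC = 0.15; above that, no number of scans from these six reaches 90% power.

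**5. What the randomisation alone supports.** Choosing 3 of 6 operators gives 20 possible allocations, so the smallest two-sided re-randomisation P is 2/20 = 0.10.

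**The case against.** **The inflation is conditional.** With no operator variation the unadjusted test stays near 5%. The comparators section says that the six are all junior fellows with broadly similar TEE experience, which argues for a modest SD. This stands: a reader might infer that the 5% error rate is simply wrong, but the document supports only that it is unprotected. In the other direction, similar experience does not mean no difference, and the Discussion itself says that routine view selection depends on the examiner's judgement and experience.

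**Patients may be shared.** Intervention description {11a} says that patients are not examined by equal numbers of operators from each group, so several operators may scan one patient. Patient effects common to both arms pull the error rate down. With patient SD 1.0 and one scan per arm per patient, it is 1.7 / 3.1 / 4.2 / 7.5% at operator SD 0 / 0.2 / 0.3 / 0.5. This also stands, although that balanced layout is a favourable case and the protocol says that numbers are unequal. Sharing patients does not remove the nesting of operator in arm.

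**The gap from 90% is not all clustering.** A reader might attribute the whole fall to 30-67% to correlated scans. Part is the 120 s cap, and at SD 0 the rest is the price of a test on 4 df.

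**The 0.10 floor is not an argument for one test over another.** A reader might take it to condemn only the unadjusted Cox test. It applies equally to the t test on 4 df, which falls below 0.05 only by assuming normality across three operators per arm.

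**An analysis plan not shown could add an operator term.** It could, but that would not make the stated 90% correct.

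**Conclusion.** The concern holds in conditional form. The randomised unit is the operator, while the stated sample size and model work at scan level as if scans were independent.

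- **Type I error:** it can exceed 5% if operators differ. It is about 7-9%, 10-11% and 17-18% at operator SD 0.2, 0.3 and 0.5, given one scan per patient, exponential times and the 120 s cap. It is about 5-6% at SD 0, and lower throughout if the same patients are scanned in both arms.
- **Power:** on the plan's own effect size and under the same assumptions, 90% is not delivered by either test. The unadjusted test has about 84-88% without operator variation because of censoring. The operator-level test has about 60-67% at SD 0 and about 30% at SD 0.5.

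The operator SD is assumed throughout, and all 46 scans are taken as usable. The documents do not support an unconditional statement that the 5% level is breached.

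**What to change.** - **Statistical methods {20a}:** base the primary inference on the operator. Either compare operator-level summaries, three against three, with t on 4 df, or fit a Cox model with an operator random effect judged against a t reference with 4 df. Add a patient term if patients are scanned by several operators. Do not use the unadjusted Cox P value for the primary claim.
- **Sample size {14}:** replace 90% with the power for 46 scans nested in six operators over a stated range of operator SDs. Show the loss from the 120 s cap separately, and say whether 36 s and 100 s are means or medians.
- **Statistical methods or Discussion:** state that with three operators per arm a two-sided re-randomisation P cannot fall below 0.10, so P < 0.05 from any test here rests on model assumptions.

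The cost is in wording and candour: wider confidence intervals, a much lower stated power and conclusions worded to match. No extra scans or staff are needed. The change makes the claim honest; it does not restore 90% power.

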### Outcomes {12}

#### Primary endpoint

The primary endpoint we define is the difference in terms of correctly discriminating causes in the phase of CPB separation within specified 120 s between the PReTEE group and the conventional TEE group. A correct diagnosis by TEE is defined as the extent of agreement up to 70% and greater between the conventional TEE/PReTEE and the expert TEE; otherwise, an uncorrected diagnosis would be accounted for.

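### The Cox model censors every failed diagnosis without separating a wrong report from no report or fixing a censoring time; coded at scan completion, the hazard ratio can favour PReTEE when it has fewer correct diagnoses by 120 s

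*Protocol article*

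**What the plan says.** The Primary endpoint section of the protocol article defines the outcome as the between-group difference in "correctly discriminating causes in the phase of CPB separation within specified 120 s". The Intervention description {11a} says what counts as failure: "If an operator does not report any diagnoses or reports the uncorrected ones, a failure will be assigned". It adds that operators leave the operating room once they have reported, so a wrong report cannot be corrected later.

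Statistical methods {20a} names a Cox proportional hazards model for diagnostic efficiency and states that "we will treat the TEE operators who failed the diagnosis as censored". It gives no censoring time and treats both kinds of failure alike. It names no other primary comparison, such as the proportions correct at 120 s.

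The Intervention description and Data collection and management both say that the study recorder measures the seconds from probe insertion to scan completion, up to a maximum of 120 s. No other time is mentioned.

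**The concern.** A scan with no diagnosis at 120 s is ordinary administrative censoring. A scan that ends at, say, 30 s with a wrong answer is different: a correct answer is no longer possible, so the wrong report is a competing event. If it is coded as censored at 30 s, it leaves the risk set as though it could still have succeeded at the same rate as the scans still running.

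The HR then compares rates of correct reports among scans not yet reported. That is a different quantity from the proportion correct by 120 s. The two can diverge most when one arm finishes sooner, which is what a three-view sequence is designed to do. The Discussion says the shorter sequence should not significantly reduce accuracy. A trade of accuracy for speed is therefore what the primary analysis must be able to show.

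**Working it through.** **The plan's own figure.** Inputs from Sample size {14}: "the time of finding out the cardiac etiologies in the PReTEE group was 36 s, whereas in the conventional group was 100 s"; "using a hazard ratio of 2.78"; "To achieve a 90% power at a significance level of 5%, 42 TEE examinations should be conducted".
- 100/36 = 2.78, which is the HR that follows from exponential times.
- Schoenfeld, two-sided 5%, 90% power, 1:1: events = 4 × (1.960 + 1.282)² / (ln 2.78)² = 42.03 / 1.045 = 40.2. This rounds to 41, or to 42 as an even number. The 42 is reproduced, as a number of events.

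**Assumptions that the documents do not settle.**
- Accuracy of reports (p_P for PReTEE, p_C for conventional) is not given. I take p_C = 90% and vary p_P.
- The protocol does not say whether 36 and 100 s are means or medians, so both are shown.
- Times are exponential and independent of correctness.
- The planned 46 scans are split 23 per arm and treated as independent.

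**HR with wrong reports censored at scan completion.** The rate of correct reports is accuracy × reporting rate, so

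HR = (p_P/36) / (p_C/100) = 2.78 × p_P/p_C.

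It stays above 1 until p_P falls below 0.36 × p_C, which is 0.36 × 90% = 32%.

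**Proportion correct by 120 s** = accuracy × P(report by 120 s).
- Medians: P(report) = 1 − 2^(−120/36) = 0.901 for PReTEE and 1 − 2^(−120/100) = 0.565 for conventional.
- Means: 1 − e^(−120/36) = 0.964 and 1 − e^(−120/100) = 0.699.

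**Accuracy below which PReTEE has fewer correct by 120 s than conventional at 90%.**
- Medians: 0.90 × 0.565/0.901 = 56%.
- Means: 0.90 × 0.699/0.964 = 65%.

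Between 32% and these values, the HR and the endpoint point in opposite directions.

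**Examples.** The last two columns give the share of simulated trials (3,000 to 4,000 per setting) significant in favour of PReTEE.

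| Times | Accuracy, PReTEE v conv. | Correct by 120 s | HR, censored at completion | Censored at completion | Held to 120 s |
|---|---|---|---|---|---|
| Medians | 50% v 90% | 45% v 51% | 2.78 × 50/90 = 1.54 | about 18% | about 2% |
| Means | 60% v 90% | 58% v 63% | 2.78 × 60/90 = 1.85 | about 35% | about 3% |
| Medians | 90% v 90% | 81% v 51% | 2.78 | about 80% | about 69% |
| Medians | 80% v 90% | 72% v 51% | 2.78 × 80/90 = 2.47 | about 67% | about 41% |

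With failures held to 120 s, the HR in the first row becomes 0.91 and in the second 1.01.

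**Where holding to 120 s is not enough.** Take lognormal times with medians 36 and 100 s, an assumed log-SD of 0.4, and accuracy 60% v 90%. Then 60.1% v 61.0% are correct by 120 s, yet the held-to-120 s HR is 1.48 and roughly 20% of trials favour PReTEE. The curves cross, so a single HR and the proportions can still disagree.

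**The case against.** The strongest objection is that the protocol states no censoring time. Coding every failure at 120 s is compatible with its text, needs no further data and removes most of the reversal. A statistical analysis plan that is not shown here may say so. This stands as a limit: a reader might infer that the plan has fixed censoring at the moment of the wrong report, and the documents do not support that. But the protocol itself sets a rule that merges the two kinds of failure, and coding the data as recorded gives the misleading version. The choice should not be left until results are known.

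A reader might also infer that the model rewards wrong answers. It does not. The HR falls in proportion to accuracy: in the median case, 90% to 50% takes it from 2.78 to 1.54. Speed is rewarded, and errors are under-penalised relative to the 120 s endpoint.

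The accuracy losses needed are large and are not documented. At 75% or 80% v 90% with medians, PReTEE really is ahead (68% or 72% v 51% correct), and both codings favour it. The rejection rates also treat scans as independent although six operators are randomised, so they illustrate the mechanism and are not this trial's operating characteristics.

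Finally, a cause-specific Cox model is a recognised analysis, and the objective mentions speed as well as accuracy. The expert's 5-point rating and the detection rates would make a collapse in accuracy visible. That is fair, but none of these is the primary test, and the stated endpoint is correctness within 120 s.

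**Conclusion.** The concern holds in this form: the censoring sentence merges a final wrong report with running out of time and leaves the censoring time open. Under the natural coding, the HR does not answer the stated primary endpoint. It can then favour PReTEE when PReTEE has fewer correct diagnoses by 120 s, at the sizes tabulated above.

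This rests on assumed accuracies, exponential times and independent scans. The reversal requires PReTEE accuracy below about 56% (medians) or 65% (means) against 90%, and it mostly disappears if all failures are coded at 120 s. The documents do not show that such an accuracy loss will occur. They also do not rule it out, and it is one of the things the trial has to find out.

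**What to change.** Replace the censoring sentence in Statistical methods {20a} with a rule for each kind of failure:
- A wrong diagnosis is a non-event that stays in the risk set to 120 s. With follow-up ending at 120 s, this is the subdistribution form.
- No diagnosis by 120 s is censored at 120 s.

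Beside the HR, report the proportion correct by 120 s in each arm with its difference and confidence interval, because crossing curves can still make the two disagree.

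The change needs one sentence and the recoding of one time variable, with no new data. The cost to state is power. Under the assumptions above with medians, it falls from about 80% to 69% at 90% v 90% accuracy, and from about 67% to 41% at 80% v 90%. With means, the latter is about 72% to 33%. The rule should be fixed before allocation is revealed to the analysts.
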